#### Treatment as usual

Treatment as usual following a presentation to one of the participating emergency departments for a suicide-related event involves a mental health Clinical Nurse Consultant recommending, or actively referring, the patient to community-based supports (e.g. general practitioner, counselling, housing support services) and may include follow up by the community mental health team. However, there is no consistent support person to help coordinate these follow ups or check whether the person has in fact connected with any community-based supports. As per local policies, TAU includes one follow-up phone call or home visit by the local health district’s mental health outreach team within seven days. A discharge letter is also sent to the patient’s nominated general medical practitioner. Other intervention services may already be in place, or arranged as part of these interactions, as required.

### Staff training

#### Peer workers

Peer workers are drawn from an established peer worker organisation (Flourish Australia). They undergo a two-day training course in relation to the Aftercare intervention, which provides education regarding the SSF-4, working with aftercare and stabilisation plans, implementing the GROW coaching model, conducting risk assessments and using escalation procedures. Four peer workers are employed by the service.

#### Mental health clinicians

Aftercare mental health clinicians are registered practitioners with the Australian Health Practitioner Regulation Agency. Three clinical psychologists, two registered psychologists and one mental health nurse are employed by the service. All clinicians have attended a four-hour training course regarding the Aftercare intervention, focusing on the development of aftercare and stabilisation plans, the use of the SSF-4, implementation of the GROW coaching model, risk assessments, and procedures for the conduct of clinical review meetings with peer workers. In addition, clinicians have completed a comprehensive online suicide prevention training course, through the Australian Psychological Society, which provides information about suicide and suicidal behaviours, training in risk assessments and crisis management, training in working with populations at serious risk of suicide, information regarding appropriate referral options, and self-care for clinicians.

### Treatment Fidelity

Intervention fidelity will be assessed by measuring treatment adherence using participant’s attendance rates for peer worker follow-up and clinician appointments. To maximise intervention integrity, documented procedures will be in place within the Aftercare service to ensure that all workers comply with the intervention protocol. Measures of service indicators, such as adherence to meeting protocols and completion of SSF-4, will be made and audited to provide an assessment of intervention integrity.

### Measurements

#### Primary outcomes

Hospital emergency department data will be extracted to evaluate the primary outcomes of likelihood of a suicide-related presentation and rate of re-presentations to the three emergency departments as a result of one or more repeat suicide attempt(s) or being at high risk for suicide. Suicide attempt or high risk for suicide will be identified by pre-determined hospital codes. Death registration data will be linked with emergency department data for participants and controls to identify deaths by any cause.

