### Study sample

Participants in the Aftercare intervention will be drawn from people who attend one of the three participating emergency departments as a result of a suicide attempt or high risk for suicide, who meet the referral inclusion criteria. Participants’ risk for suicide (and therefore suitability for the Aftercare intervention) will be determined by the hospital staff using standard mental health assessment protocols. Those considered for referral to the Aftercare intervention will be 16 years of age and over. Those excluded from consideration for the service will be admitted to the hospital as an inpatient, or being actively case managed by mental health services, at that time of presentation to the emergency department. Those who consent to participate in the Aftercare intervention and who consent for their data to be included in the study will form the intervention group for the study.

The control group (TAU) will be sourced via de-identified hospital data extraction. They will be people 16 years of age and over who attend a participating emergency department as a result of a suicide attempt or high risk for suicide but either do not receive, or do not accept, a referral to the Aftercare intervention (i.e. did not wish to participate in the service; were unable to participate for other reasons e.g., time commitments; or had not received a referral to the service e.g. standard procedures were not followed in the emergency department). Pre-determined hospital codes for suicide attempt or high risk for suicide will identify controls. They will be selected by identifying those patients who presented to any of the emergency departments in the study during the study period, and identifying those who presented in the same month, who met the study inclusion criteria, and who had the closest emergency department presentation dates to the participants undertaking the Aftercare intervention and enrolled in the trial*.* A human research ethics waiver for consent was granted; all data is sourced via hospital data and code sets.

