### Data analysis

Analyses will be conducted using the Statistical Package for the Social Sciences version 25 [85] and SAS v9.4 [86]. Primary analyses will be conducted according to the intention-to-treat approach. Presentations to an emergency department with a repeat suicide-related event and for all-cause death will be compared between the two non-randomised groups (intervention vs control) using a Kaplan Meier plot where the initial presentation to an emergency department is designated as time zero, and using censoring. A log-rank test will compare the Kaplan Meier curves of the two groups.

A negative binomial regression model will be applied to the data to estimate the effect of the intervention on re-presentation rates, accounting for varying lengths of follow-up period and adjusting for service and person-level characteristics (e.g. facility, age, sex, indigenous status) and censoring.

To investigate the impact of the service on suicide risk factors (secondary outcome measures), a comparison of pre- and post-intervention outcome measures will be conducted for participants of the intervention using paired t-tests, or a Wilcoxon signed-ranks test (if the sample is non-normally distributed), adjusting for multiple comparisons (Bonferroni correction).

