### Sample size and statistical power

The sample size required to achieve power of 80% was estimated for the primary analyses using G*Power [87]. Local hospital data (2014/2015 year) indicated that approximately 1340 people present to emergency departments with suicide-related presentations annually and systematic reviews have estimated that 16% re-attempt suicide within 12 months [5]. Based on Hvid et al.’s [30] report that an intervention group had approximately half the rate of deaths by suicide than a TAU group at 12 months (.087 vs .219), the sample size required for a log-rank test at α level .05 is 75 participants in the intervention group and 1265 participants in the control group.

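### Controls are selected by the kind of hospital code that later counts as the event, while participants have no stated index-code condition, so repeat presentations may be detected more often in controls

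*Protocol article*

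**What the plan says.** Three statements in the protocol article matter here.

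- **Outcome.** Under Primary outcomes, repeat presentations in both groups are taken from emergency department data, and "Suicide attempt or high risk for suicide will be identified by pre-determined hospital codes". Mortality has a different source: "Death registration data will be linked with emergency department data for participants and controls to identify deaths by any cause".
- **Control entry.** Under Study sample: "Pre-determined hospital codes for suicide attempt or high risk for suicide will identify controls".
- **Participant entry.** The same section says that a participant's suicide risk, and so suitability for the service, "will be determined by the hospital staff using standard mental health assessment protocols". It continues: "Those who consent to participate in the Aftercare intervention and who consent for their data to be included in the study will form the intervention" arm. No hospital code at the index visit is stated as a condition for this arm.

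On analysis, the Data analysis section says "A log-rank test will compare the Kaplan Meier curves of the two groups" and states no covariates for that test. The negative binomial model for re-presentation rates is described as "adjusting for service and person-level characteristics (e.g. facility, age, sex, indigenous status) and censoring". The Limitations section discusses self-selection of participants but not any difference between the arms in how events are ascertained.

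**The concern.** The hospital code is the measuring instrument for hypotheses 1 and 2. Every control has, by construction, already given one positive reading on an instrument of that description. On the text as written, a participant need not have done so, because a clinician's judgement and a referral are enough.

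Suppose some suicide-related visits are coded as something else, and the tendency to be coded is similar across visits of the same person or the same type of presentation. A person coded once is then more likely than average to be coded again. Selecting controls on a coded index visit would raise the detection of their later visits relative to participants. With identical true re-presentation in the two arms, the intervention arm would show fewer counted events, a higher Kaplan-Meier survival curve and a rate ratio below 1.

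This is distinct from self-selection, since it could occur in clinically identical groups. The unadjusted log-rank test does nothing about it. In the rate model, facility could absorb differences in coding between hospitals, but the listed covariates would not remove differences by person or presentation type.

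**Working it through.** **The plan's own figure.** The Sample size section states that "the sample size required for a log-rank test at α level .05 is 75 participants in the intervention group and 1265 participants in the control" arm, for 80% power with 12-month proportions .087 and .219. A two-sided, continuity-corrected comparison of two proportions at that allocation gives 75 in the intervention group, which matches. Without the continuity correction, 75 vs 1265 has 85.7% power. The point does not rest on this figure; it is used only to cost the fix.

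**Detection model (assumed; the protocol gives no coding sensitivity).** Let s be the mean probability that a suicide-related visit receives one of the codes, and r the correlation of coding between visits of the same person.

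- Later visit coded, given index coded (controls): s + r(1 − s).
- Later visit coded, with no selection on the index code (participants): s.
- Ratio of detected events under no true effect: s / [s + r(1 − s)].

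Example: s = 0.7, r = 0.3 gives 0.70 / (0.70 + 0.3 × 0.30) = 0.70 / 0.79 = 0.886.

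| s | r = 0 | r = 0.1 | r = 0.3 | r = 0.5 |
|---|---|---|---|---|
| 0.9 | 1.00 | 0.99 | 0.97 | 0.95 |
| 0.7 | 1.00 | 0.96 | 0.89 | 0.82 |
| 0.5 | 1.00 | 0.91 | 0.77 | 0.67 |

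**Chance of a false finding of benefit.** This uses 75 vs 1265 and a two-sided .05 test of two proportions as a stand-in for the log-rank test; the nominal chance in the favourable tail is 2.5%. With a true 12-month risk of 16% (the repeat-attempt figure in the Sample size section), s = 0.7 and r = 0.3, the detected risks are 0.16 × 0.70 = 0.112 and 0.16 × 0.79 = 0.1264.

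- Standard error under the null (pooled risk 0.1256): √[0.1256 × 0.8744 × (1/75 + 1/1265)] = 0.0394.
- Standard error under the detected risks: √[0.112 × 0.888/75 + 0.1264 × 0.8736/1265] = 0.0376.
- z = (0.0144 − 1.96 × 0.0394) / 0.0376 = −1.67, so the chance is 4.7%.

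The same steps give 2.7% at s = 0.9, r = 0.1 and 14.1% at s = 0.5, r = 0.5. With a true risk of 21.9%, the s = 0.7, r = 0.3 and s = 0.5, r = 0.5 cases give 5.6% and 20.5%.

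**How the result depends on the participants' coded share.** The table implicitly sets the share of participants coded at index, c, equal to s. More generally, a person not coded at index has later detection s(1 − r), so participants' detection is c[s + r(1 − s)] + (1 − c)s(1 − r).

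- s = 0.7, r = 0.3, c = 0.90: 0.9 × 0.79 + 0.1 × 0.49 = 0.760; ratio 0.760 / 0.79 = 0.96.
- s = 0.7, r = 0.3, c = 0.95: 0.95 × 0.79 + 0.05 × 0.49 = 0.775; ratio 0.98.
- s = 0.5, r = 0.5, c = 0.90: 0.9 × 0.75 + 0.1 × 0.25 = 0.700; ratio 0.700 / 0.75 = 0.93.
- c = 1: ratio 1.00 for any s and r.

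**Power of a code-filtered comparison** at .087 vs .219, with 1265 controls, two-sided and without continuity correction:

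| Participants retained | Share of 75 | Power |
|---|---|---|
| 75 | 100% | 85.7% |
| 68 | about 90% | 81.4% |
| 60 | 80% | 75.2% |
| 53 | about 70% | 68.4% |
| 38 | about 50% | 49.5% |

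**The case against.** The strongest reply is that this argues from silence. Both arms are drawn from people attending for a suicide attempt or high risk, the article condenses a longer protocol, and how a participant's index visit is located in the extract may be settled there. Participants have also had a mental health assessment and been judged at enough risk to refer, so they may well be coded more often than an unselected attender. That stands, and it shrinks the effect markedly, as the calculation with c = 0.90 shows.

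The direction is not assured either. With independent coding between visits there is no differential detection. If recognised participants are coded as reliably as controls, the gap vanishes; if more reliably, it reverses. Controls coded as suicidal in error would tend to lower the control event rate, which works the other way. For hypothesis 2, facility adjustment may deal with the between-hospital part.

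A reader might infer that the design builds in a spurious benefit, or that participants lack the code. The documents support neither: they do not say that participants are uncoded, and they give no sensitivity, specificity or between-visit correlation.

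What survives is narrower. The two entry routes and the outcome definition are stated in the article itself. Only one route is explicitly conditioned on the code, and neither the log-rank test nor the Limitations section deals with the difference.

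**Conclusion.** The asymmetry is in the text; the bias is conditional. Repeat presentations may be detected more often in controls, pushing hypotheses 1 and 2 towards benefit, if coding is imperfect, if it persists across visits within a person or presentation type, and if a material share of participants is uncoded at index. All three are needed. Hypothesis 3 is untouched.

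The range of 1.00 to 0.67 for the null ratio reflects assumed values only. The lower end needs half of suicide-related visits to be missed and a correlation of 0.5. Under the milder assumptions the distortion is at most about 11%, small beside the planned ratio of .087/.219 = 0.40, though it would nearly double the chance of a false positive at 16% risk. Whether the matter is live depends largely on one number that the linked data can supply: the share of participants whose index visit carries one of the codes.

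**What to change.** Add one paragraph to the analysis text with three parts.

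1. From the linked extract, report the share of participants whose index emergency presentation carries one of the pre-determined codes.
2. Pre-specify a sensitivity analysis for hypotheses 1 and 2 that compares index-coded participants with controls, so that the same filter applies to both arms.
3. Keep the all-participant intention-to-treat comparison as primary, and qualify any claim of benefit if the two analyses differ materially.

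The data cost is one added field. Linkage of service and hospital identifiers is already planned, and each participant's initial presentation has to be located anyway because it is time zero.

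The statistical cost is precision in the filtered analysis, in proportion to the uncoded share: power at the planning rates falls from about 86% to 75% if 80% of participants are coded, and to 68% if 70% are. For that reason, and because a code-restricted subset would displace the stated intention-to-treat approach, the filtered comparison should not become the deciding analysis. If the coded share is close to 100%, the two analyses nearly coincide, the concern falls away and almost nothing is lost.

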#### Secondary outcomes

Secondary outcome measures were chosen as they assess factors associated with increased risk for suicide [64–68]. The measures will be collected from the participants of the Aftercare intervention (pre- and post-) using the following measures.

#### Hopelessness

The short form of the Beck Hopelessness Scale (BHS-SF) [72] is derived from the original Beck Hopelessness Scale [73] and consists of four True/False items designed to measure hopelessness in the past week. An example of an item is “I might as well give up because I can’t make things better for myself”. The BHS-SF has demonstrated high internal consistency (α = .85) and has been found to be positively correlated with dysfunctional attitudes, exhaustion, psychological distress, hostility, lack of life goals and inability to cope emotionally [72].

#### Belongingness and burdensomeness

The 15-item Interpersonal Needs Questionnaire (INQ) utilises a seven-point Likert Scale (1 = not at all true for me, 7 = very true for me) designed to measure thwarted belongingness and perceived burdensomeness [74]. An example of an item measuring thwarted belongingness is “These days I am fortunate to have many caring and supportive friends” (reverse scored). An example of an item measuring burdensomeness is “I think my death would be a relief to the people in my life”. Both the thwarted belongingness and perceived burdensomeness scales have shown good internal consistency (α = .85 and α = .89, respectively) and have been found to demonstrate criterion validity [74, 75].

#### Depression, anxiety and stress

The 21-item version of the Depression, Anxiety and Stress Scales (DASS-21) [76] measure items on a four-point Likert Scale (0 = did not apply to me at all, 3 = applied to me very much or most of the time) designed to gauge symptoms of depression, anxiety and stress. The DASS-21 has an acceptable level of internal consistency with Cronbach’s alphas for the three scales ranging from .73 (anxiety) to .81 (depression and stress) [77]. The DASS-21 has been well validated [78–80]. The depression scale of the DASS-21 has been found to predict suicidal ideation [81].

#### Psychological distress

The 10-item Kessler Psychological Distress Scale (K-10) [82] consists of 10 items rated on a five-point scale Likert Scale (1 = none of the time, 5 = all of the time) designed to measure psychological distress over the past four weeks, e.g., “About how often did you feel so nervous that nothing could calm you down?” The K-10 has demonstrated good reliability and validity [83].

### Data handling

Primary outcome data of re-presentations to an emergency department and other local health district data on hospital admissions, community mental health and mental health outcomes will be extracted and de-identified by the Centre for Health Research Illawarra Shoalhaven Population (CHRISP), a research centre which performs data linkage through a partnership between the local health district and the University of Wollongong. Deaths attributable to any cause will be obtained from NSW death registration data held by the NSW Centre for Health Record Linkage (CHeReL). The researchers with be provided with the de-identified coded data.

Secondary outcome data (suicide risk factors) will be collected by the Aftercare service prior to the participant attending their initial session with a mental health clinician and again at the time of their final (discharge) session with the clinician. For Aftercare participants who consent for their data to be included in the study, the data will be de-identified and coded within the Aftercare service, prior to being provided to the researchers.

Data transfers and storage will comply with national and state legislation, national ethics principles and University of Wollongong, local health district and the CHRISP data management policies.

#### Data linkage

The CHRISP data integration officer will link Aftercare and local health district identifiers using deterministic linkage on the Illawarra Health Information Platform. CHeReL will link CHRISP’s patient identifier with their own patient identifier using deterministic linkage in the first instance, and probabilistic linkage if required. Probabilistic record linkage allows a calculation of the probability of a match between two or more records to be made when the records are not exactly identical in one or more of the participant identifier fields (e.g., surname ‘Browne’ or ‘Brown’). A record linkage is determined by set thresholds for acceptable probability [84]. Non-identifiable local health district data will be provided to the researchers by CHRISP. Non-identifiable Aftercare service data will be provided to the researchers by the Aftercare service. Non-identifiable deaths data from the state’s Registry of Births, Deaths and Marriages will be provided to the researchers by CHeReL.

### Data analysis

Analyses will be conducted using the Statistical Package for the Social Sciences version 25 [85] and SAS v9.4 [86]. Primary analyses will be conducted according to the intention-to-treat approach. Presentations to an emergency department with a repeat suicide-related event and for all-cause death will be compared between the two non-randomised groups (intervention vs control) using a Kaplan Meier plot where the initial presentation to an emergency department is designated as time zero, and using censoring. A log-rank test will compare the Kaplan Meier curves of the two groups.

A negative binomial regression model will be applied to the data to estimate the effect of the intervention on re-presentation rates, accounting for varying lengths of follow-up period and adjusting for service and person-level characteristics (e.g. facility, age, sex, indigenous status) and censoring.

To investigate the impact of the service on suicide risk factors (secondary outcome measures), a comparison of pre- and post-intervention outcome measures will be conducted for participants of the intervention using paired t-tests, or a Wilcoxon signed-ranks test (if the sample is non-normally distributed), adjusting for multiple comparisons (Bonferroni correction).

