### Study design

A controlled non-randomised two group (intervention vs treatment-as-usual (TAU) control) design will be used to test the primary hypotheses (hypotheses 1–3), following the intention-to-treat method. The secondary objectives of the study will be evaluated using a pre- and post-intervention repeated measures design (hypothesis 4), in which the intervention group (i.e. participants of the Aftercare intervention) will complete self-report questionnaires prior to their initial intervention session, and again at the time of their discharge appointment from the service.

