### Study procedure

Health consumers attending their local emergency department following a suicide attempt or at high risk for suicide are provided with a mental health assessment by clinical staff, where risk for suicide (and therefore suitability for the Aftercare intervention) is determined by standard hospital mental health assessment protocols. Staff determine whether the consumer warrants admission to hospital, as per the NSW Ministry of Health policies. If the consumer is not admitted to hospital as an inpatient, standard procedures include one follow-up phone call or home visit by the local health district’s mental health outreach team within seven days and a discharge letter to the person’s general practitioner. If the consumer is eligible for referral to the Aftercare service he/she will also be given a brief overview of the service by an emergency department clinician and at that time may choose to provide verbal consent to be referred to the service. The emergency department staff will contact the Aftercare service by phone and provide a referral. The participant flow process is shown in Fig. 1.

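### The primary analyses are labelled intention-to-treat, but the groups are formed by uptake and consent, so the plan compares consenting participants with non-participants

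*Protocol article*

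**What the plan says.** The intention-to-treat claim appears twice in the protocol article. Study design applies it to the primary hypotheses ("following the intention-to-treat method"), and Data analysis states: "Primary analyses will be conducted according to the intention-to-treat approach".

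Study sample defines the groups. The intervention group is "Those who consent to participate in the Aftercare intervention and who consent for their data to be included in the study". Controls are people with a qualifying presentation who "either do not receive, or do not accept, a referral to the Aftercare intervention". The examples given for controls include people who "did not wish to participate in the service; were unable to participate for other reasons e.g., time commitments", as well as people who were never referred. Controls come from de-identified hospital data under a consent waiver.

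Study procedure has the patient hear about the service in the emergency department, where he or she "at that time may choose to provide verbal consent to be referred to the service". Under Aftercare intervention, the research information sheet and consent form come later, around the first community appointment.

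Study aims words hypotheses 1 to 3 as participants against non-participants. Limitations concedes that participants select themselves. Neither section qualifies the intention-to-treat claim.

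**The concern.** Without randomisation, an intention-to-treat claim can still mean something useful: everyone to whom the service was directed is analysed together, whether or not they took it up. That removes one source of selection, the patient's own decision to engage. The groups defined under Study sample do not have this property, because the patient's decisions to accept and to consent determine the group. Only the intervention group is filtered on those decisions; the controls enter by waiver.

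All three primary hypotheses are affected. A result labelled intention-to-treat could be taken to speak to the effect of offering the service, which is the policy question. The comparison as defined speaks only to people who took part, set against a mixture of people who refused and people who were never asked.

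**Working it through.** **1. Who goes where.** The documents give no uptake, refusal or no-show figures, so the main check is of definitions. (The stated 75 and 1265 can be reproduced with a continuity-corrected two-proportion formula on 0.087 vs 0.219, two-sided; this has no bearing on the point.)

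| Patient | Group under Study sample | Group if analysed by offer |
|---|---|---|
| Never offered referral | Control | Not offered |
| Offered, declined | Control (explicit) | Offered |
| Accepted referral, never attended | Unclear | Offered |
| Used the service, withheld data consent | Neither | Offered |
| Gave both consents, stopped early | Intervention (no rule moves them) | Offered |
| Gave both consents, completed | Intervention | Offered |

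The second row is an express departure from analysis by offer. The fourth follows from the definition: these people accepted referral, so they are not controls, and they did not give the second consent, so they are not in the intervention group. No step is described that would keep them out of the control extraction, which works from hospital codes and presentation dates. The third row can be read two ways. Taken literally, people who accepted referral are not controls; but the example of being unable to take part for other reasons may cover them. On either reading, uptake decides.

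**2. Whether the analysis compensates.** Data analysis compares the Kaplan-Meier curves with a log-rank test that has no covariates. The negative binomial model for re-presentation rates adjusts for characteristics such as hospital site, age, sex and Indigenous status. None of these examples measures willingness to engage.

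**3. What selection alone could do (all risks assumed).** Suppose the service has no effect. Let participants, decliners and never-offered patients have 12-month risks P, D and N, and let a share d of controls be decliners. The plan's risk ratio is P / [d×D + (1−d)×N].

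- P = 12%, D = 20%, N = 16%, d = 0.5: 12/(10 + 8) = 12/18 = 0.67. For d = 0.25 it is 12/17 = 0.71; for d = 0.75, 12/19 = 0.63.
- Swap the first two, P = 20%, D = 12%, N = 16%, d = 0.5: 20/(6 + 8) = 20/14 = 1.43. For d = 0.25 it is 20/15 = 1.33; for d = 0.75, 20/13 = 1.54.
- All three equal: 1.00.

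**4. People who accept but are not analysed (assumed).** Suppose again no effect and a risk of 0.219 both in controls and on average among accepters. A share q of accepters drops out of the analysed group, with m times the risk of those who stay. The analysed intervention risk is 0.219 / [(1−q) + q×m].

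- q = 0.1, m = 1.25: 0.219/1.025 = 0.214, ratio 0.98.
- q = 0.5, m = 2: 0.219/1.5 = 0.146, ratio 0.67.
- m = 1: ratio 1.00. For m below 1 the ratio exceeds 1.

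**5. Scale.** The planned contrast is 0.087/0.219 = 0.40. A spurious 0.67 would be ln(0.667)/ln(0.397) = 0.405/0.923, about 44% of the planned effect on the log scale.

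**6. Dilution if accepters were analysed together (assumed).** If a share q of accepters received no service and kept a risk of 0.219, the group's risk would be (1−q)×0.087 + q×0.219. That is 0.100 at q = 0.1 and 0.153 at q = 0.5, so the ratio moves from 0.40 to 0.46 and 0.70.

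**The case against.** The best defence is that, in a non-randomised study, intention-to-treat may simply mean that everyone enrolled is kept whatever their adherence. The text is compatible with this: Treatment Fidelity uses attendance to measure adherence, and nothing removes or reclassifies enrolled people who attend poorly. The hypotheses are openly about participation, and Limitations discloses self-selection. This carries weight, but the protocol never states the narrower meaning, and neither the hypotheses nor the limitation corrects the label.

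Several stronger readings are tempting and are not supported:

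- *The comparison is as-treated.* Membership rests on two consents, not on sessions received, and enrolled people who stop early appear to stay in their group.
- *Attending the first appointment is an entry criterion.* That is a plausible inference from when consent is sought, but it is not a stated rule.
- *No-shows fall in neither group.* The wording on being unable to take part may make them controls, and the participant flow figure, which is not shown, may settle it.
- *The design favours the service by a known amount.* The 0.67 rests wholly on assumed risks; the documents give no outcome risk by uptake.
- *Readers will necessarily take the result as the effect of the offer.* The participation wording is visible to them.
- *An analysis by offer is readily available.* Referral is telephoned through after verbal consent, so a refusal in the emergency department may leave no record. Never-offered patients are not a random group either, since they include cases where usual procedure lapsed.

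**Conclusion.** The point stands as a mismatch between the stated analysis principle and the stated group definitions. What is planned is a comparison of all consenting participants, regardless of later adherence, with non-participants, some of whom refused the service. Allocation is by uptake, whichever way the no-shows are counted. The comparison is open to selection bias, and the log-rank test leaves it unaddressed.

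Neither size nor direction can be derived from the documents. The illustrations run from 0.63 to 1.54 with no true effect and depend entirely on the assumed risks and shares. There is no bias from these sources if decliners, no-shows and non-consenters carry the same risk as participants and never-offered patients. The illustrations show only that selection could be large relative to the planned effect. It does not follow that the result is biased in favour of the service.

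**What to change.** 1. Under Study design and Data analysis, replace the intention-to-treat claim with: *comparison of all enrolled consenting participants, regardless of adherence, with non-participants*. Limit the conclusion to participation, not the effect of offering the service.
2. State where people who accept referral but never attend, and service users who withhold data consent, are counted. Keep known service users out of the control extraction.
3. Where hospital or service records and approvals identify offer status, add sensitivity analyses: participants against never-offered and against declined controls separately, and offered against never-offered. Report that the last remains non-randomised and is diluted by non-uptake.

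The first item and the statement in the second cost only wording. Excluding non-consenting service users from the extraction needs a flag applied before de-identification and may need an ethics note. The third depends on whether declined offers are recorded, which the protocol does not describe; if they are not, it should be reported as not feasible. The primary comparison and recruitment target need not change.
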